## Abstract

**Background:**

Chronic wounds, those which have not healed in a timely manner, are a significant health and economic burden. Older people, especially those living in nursing homes, are disproportionately affected by chronic wounds, and effective management and prevention is a persistent challenge. Specialized wound care can improve outcomes; however, access is limited by aged care workforce shortages, fragmented care, and lack of local services, especially in rural and nursing home settings. Virtual wound care interventions such as WoundView (Coviu Global Pty Ltd), a novel computer vision–based artificial intelligence wound analysis app embedded in Coviu’s existing telehealth platform, offer a potential solution to enhance engagement with specialized wound care services.

**Objective:**

This protocol aims to outline a pilot and feasibility study for WoundView to assess the acceptability and feasibility of the intervention in preparation for a planned implementation study. The pilot and feasibility study will estimate recruitment and retention rates along with protocol adherence and adaptations. Qualitative exploration of the acceptability of recruitment processes, training and education, participant assessments, intervention delivery, and secondary outcome measures will inform the development of an implementation study of WoundView.

**Methods:**

The WoundView pilot and feasibility study is a prospective, nonrandomized study in 2 nursing homes in New South Wales, Australia. The research population will comprise up to 10 nursing home residents, 10 to 30 nursing home staff, and 10 wound care clinicians. All resident participants will receive the intervention, WoundView, as routine clinical care throughout the study period. Virtual care will be conducted with a specialized wound care clinic using WoundView’s wound analysis and telehealth features to guide the clinical management of chronic wounds. Wound measures, health-related quality of life, virtual care activity, hospitalization rates, health resource use case studies, and participant satisfaction will be assessed. Nursing home staff and wound care clinicians’ satisfaction with WoundView will be collected through brief surveys and in-depth interviews.

**Results:**

The WoundView pilot and feasibility study was approved by the university’s ethics committee and registered on the Australian New Zealand Clinical Trial Registry. Recruitment and enrollment for the study began in May 2025. Results are expected in the second half of 2025.

**Conclusions:**

The design and implementation of virtual care interventions in nursing homes is an underinvestigated issue. Outcomes from this study will contribute to the design of an implementation study testing WoundView in a range of nursing homes around Australia. The integration of WoundView is expected to transform the use of virtual care for wound management and lead to earlier intervention and increased access to specialist wound advice services for nursing home residents.

## Introduction

### Background

Chronic wounds present a major public health challenge with significant health and economic costs [1]. Chronic wounds are those that have not progressed through the normal stages of healing in a timely and organized process [2] and substantially reduce the quality of life of those affected [3]. The most common types are pressure injuries and chronic lower leg wounds, including diabetic, venous, and arterial ulcers [4]. The global burden of skin and subcutaneous diseases has risen rapidly over the last 15 years, but the lack of international prevalence data for chronic wounds limits the ability to estimate true impact [5]. Based on available figures, an estimated 2.5% of Americans are affected by chronic wounds, the majority of whom are older adults [6]. In Australia, the prevalence of chronic wounds is estimated at 1.9% [7] and accounts for Aus $6.6 billion (US $4.29 billion) per year in costs to health and aged care budgets [8]. Between 2013 and 2017, more than two-thirds of people with chronic wounds who were admitted multiple times to public hospitals in the Australian state of New South Wales (NSW) were aged 65 years or older [9].

Older people, with increasing frailty, impaired skin integrity, and comorbidities such as diabetes, obesity, and peripheral vascular disease, are disproportionately affected by chronic wounds [10,11]. Chronic wounds are particularly common among residents of nursing homes, with an estimated prevalence of pressure injuries of up to 26% [12]. Despite being common, less than 1 in 5 of those with pressure injuries had a wound management record documenting every current injury in a 2018 NSW study of 67 nursing homes [12]. Inadequate wound prevention and treatment was also emphasized by the 2021 Australian Royal Commission into Aged Care Quality and Safety as causing pain, distress, and premature death [13]. Aged care staff giving evidence at the commission reported inadequate knowledge and training in managing pressure injuries effectively [13]. Despite the commission’s recommendation that wound care training and education be improved, inadequate wound care continues to be one of the most common clinical complaints made to the Australian Aged Care Quality and Safety Commission [14].

Evidence-based wound care can improve clinical outcomes of chronic wounds [15]; however, provision of such care in nursing homes can be challenging. Wound care is a specialized field, and in aged care, there is higher variance in wound management and less specialist wound oversight than in other settings [10]. Chronic workforce shortages, high staff turnover, variable wound care expertise among staff, and fragmented and untimely access to expert wound care also limit the provision of consistent and high-quality wound care [13]. Along with evidence-based care, access to clinicians with expertise in wound management can ensure high-quality care and improve resident outcomes; however, in Australia, specialized wound care clinics are generally confined to major centers, which limits in-person attendance by rural and immobile nursing home residents [16]. This geographic centralization of wound care services creates significant barriers to timely assessment and treatment, contributing to delayed wound healing and avoidable complications [17].

Virtual care, health care delivered remotely using information and communication technology services [18], can address access barriers to ensure personalized and timely health care [19] for those unable to attend in-person wound clinics, such as nursing home residents. While the terms virtual care and telehealth are frequently used interchangeably, virtual care is a broader term encompassing telehealth (video or telephone consultations), remote patient monitoring, store-and-forward communications, and website and mobile apps [20]. Virtual care has demonstrated safety and effectiveness in wound healing and can overcome access gaps in chronic wound care [21,22]. Virtual wound care trials have also shown reductions in wound healing times and wound-related hospitalizations [23]; however, there have been few studies undertaken in nursing homes [24]. Furthermore, while current virtual wound care interventions offer wound analysis and measurement capabilities, they lack seamless integration with video telehealth platforms, restricting their effectiveness in remote care.

The number of Australians living in permanent aged care is growing, with 178,000 people aged 65 years or older residing in aged care in 2022, a 3.1% increase since 2017 [25]. Australia has among the highest proportions of older people living in permanent aged care when compared with other similar countries, including the Netherlands, Japan, and Canada [26]. Despite increasing numbers of nursing home residents, there has been a 5.2% drop in aged care providers, attributed to regulatory and financial pressures [27]. To meet the industry’s growing demands and address the imminent implementation of the strengthened Aged Care Quality Standards [28], virtual care innovation, such as artificial intelligence (AI) to assist with wound analysis and remote consultation, is needed to transform the aged care sector, meet the needs of consumers, and improve care outcomes [27]. One such virtual care solution is WoundView, a new AI wound analysis application embedded in an existing telehealth platform, Coviu, which aims to address access barriers to evidence-based and specialized wound care.

### WoundView Application

A 5-year, multipartner research project funded by the Australian Government’s Medical Research Future Fund has developed the WoundView application (here referred to as WoundView) to improve access to specialized wound care in nursing homes and other remote settings. WoundView uses a computer vision–based AI algorithm that has been developed and validated using more than a thousand wound images. WoundView produces wound bed segmentation and measurements (ie, length, width, and total area), which can be monitored and compared over time. WoundView (Figure 1) is embedded in the existing telehealth platform, Coviu, allowing for real-time video telehealth between nursing home residents and staff and external wound clinicians. The Coviu platform enables the video call component of the Australian Government–funded Healthdirect Australia, the national virtual public health information service, enabling telehealth use in Australian nursing homes at no cost.

**Figure 1. F1:**
[figure not shown]
Visualization of WoundView use (reproduced from Coviu Global Pty Ltd [29] and Unsplash [30]). AI: artificial intelligence.

WoundView uses consumer-grade, hand-held devices, including mobile phones, laptops, and tablet devices to assess chronic wounds. The Coviu platform delivers secure, web-based video telehealth. It does not require the download of an app, and all transmitted call data, including images and documents, are transmitted peer-to-peer (ie, between call participants) and protected with end-to-end encryption [31]. This protocol describes a pilot and feasibility study to assess the acceptability and feasibility of WoundView for residents and staff working in nursing homes and external wound care clinicians in NSW, Australia.

### Objectives

The primary objective of the pilot study is to assess the feasibility and acceptability of the proposed approach in preparation for an implementation study on WoundView. Study recruitment and retention and protocol adherence and adaptations will be used to evaluate the primary objective. The secondary objectives are to assess the acceptability of data collection tools for possible inclusion in the implementation study and evaluate collected wound images to verify and update the WoundView AI wound analysis algorithms for future use in nursing homes.

## Methods

### Study Design

The WoundView pilot and feasibility study is a prospective, nonrandomized trial in which all residents with a chronic wound will be eligible to receive the intervention, WoundView. Use of WoundView will be facilitated by staff working at pilot site nursing homes, and wound care will be provided by the Wound Care Command Centre (WCCC) or usual wound care providers. Nursing home staff, WCCC clinicians, and usual wound care providers who use the intervention will also be invited to participate in the study.

The study will determine the acceptability of WoundView and assess the feasibility of selected outcome measures in preparation for an implementation study. The pilot and feasibility study will be reported using the CONSORT (Consolidated Standards of Reporting Trials) extension to pilot and feasibility trials Checklist 1 [32], SPIRIT (Standard Protocol Items: Recommendations for Interventional Trials) statement Checklist 2 and additional guidance on reporting of nonrandomized pilot and feasibility studies by Lancaster and Thabane [33]. A mixed methods approach will be used to assess acceptability and feasibility.

The study will involve 2 phases (Figure 2). During Phase 1, staff working in the pilot site nursing homes will be upskilled in general telehealth and trained to use WoundView. Phase 2 will pilot WoundView and assess the feasibility of the trial design for the planned implementation study.

**Figure 2. F2:**
[figure not shown]
Proposed research plan in 2 phases.

### Setting

The study will be conducted in 2 private, not-for-profit nursing homes in NSW, Australia. One site is an 80-bed facility in outer regional NSW, as defined by Australian Statistical Geographical Standard Edition 3 [34]. The second site is a 140-bed facility in Sydney, NSW, a major city [34]. The pilot study nursing home sites will be supported by either the WCCC, a team of specialized nurses at the Royal Prince Alfred Virtual Hospital based in Sydney, Australia, or their usual wound care provider.

### Participants

The study will recruit three participant groups: (1) nursing home residents living with chronic wounds, (2) nursing home clinical staff involved in wound care (eg, registered nurses, enrolled nurses, and wound care coordinators), and (3) WCCC clinicians and usual wound care providers, (eg, wound care nurses and general practitioners) who are providing specialized wound care using WoundView.

#### Residents

All residents living in the nursing home pilot sites who have or develop a chronic wound during the study period, regardless of wound type, will be eligible to participate. It is estimated that the number of participants across both sites will be 6 to 10 residents based on wound burden, number of eligible residents, and the relatively brief intervention period of 4 months.

Recruitment will be undertaken using purposive sampling, where participants who meet the eligibility criteria will be consecutively enrolled into the study. Once enrolled, WoundView will be used to collect and analyze wound images and connect residents to specialized wound management. Resident eligibility criteria are described in Textbox 1 and the participant flow is outlined in Figure 3.

Uncited Textbox 1.Nursing home resident eligibility criteria.
**Inclusion criteria**
Adults aged 18 years or olderWilling and able to give informed consent for participation in the studyHave a chronic wound at the start or develop a chronic wound during the study period. A chronic wound is defined as a wound that has been present for 3 or more weeks OR is likely to take 3 or more weeks to heal [35] as determined by nursing home staff and managers with clinical experience in wound careWound must be considered suitable for active treatment as per the advice of the nursing home staff
**Exclusion criteria**
Cognitive impairment that affects the ability to provide informed consent as determined by the nursing home staff or managers and research team at the point of enrolmentSensory, physical, or other health impairment that would preclude data collection participation, as determined by the nursing home staff or managers and research team at the point of enrollment. Other health impairment includes residents who are reliant on medications, for example, participants receiving medication to support end-of-life care or participants with severe mental health conditions where the condition is not adequately controlled by medication at the time of recruitment.Have superficial, rapidly healing wounds such as abrasions, blisters, or lacerations.Chronic wound located on the genital areaNot fluent in spoken or written English

**Figure 3. F3:**
[figure not shown]
Participant flow diagram.

Nursing home staff and managers will be asked to identify residents who meet the study eligibility criteria (Textbox 1). Following the identification of potential participants, the research team will approach the resident to explain the study’s nature, purpose, and procedures along with expected duration and potential risks and benefits. Potential participants will be provided with a research information sheet and consent form. Residents will be invited to discuss their potential participation with support people such as next of kin, family, friends, or their enduring guardian. Following a 3-day cooling-off period, the research team will contact the resident to ascertain their preference to be involved in the study. To avoid perceived or actual coercion, recruitment and consent will be undertaken by the research team, who are independent of the nursing home.

Nursing home residents who verbally consent to participate will be invited to provide written consent at the beginning of the study. Throughout the study, WoundView will be used as routine clinical care, and further consent will not be sought for each episode of use of WoundView in wound management. At the conclusion of the study, residents will be invited to reconfirm their consent verbally, prior to the final data collection.

Resident participants may withdraw from the research study at any time on request, with assurance that their withdrawal will not affect their relationship with their nursing home or the university. To avoid perceived or actual coercion, written consent of nursing home residents will be undertaken by the research team, who are independent of the nursing home. Participants will not receive any payment or reimbursement for their participation.

#### Nursing Home and WCCC Clinicians

All clinical staff working at the participating nursing homes, WCCC clinicians, and usual wound care providers are eligible to participate if they are aged 18 years or older and can undertake data collection in English.

During Phase 1, telehealth and WoundView education and training will be conducted with nursing home staff nominated by their organization to participate. Nursing home staff will be provided with access to a curated package of self-directed online telehealth videos [36], which will take approximately 20 to 30 minutes to complete. Following telehealth training, face-to-face WoundView training will be conducted by the research team, lasting 30 to 45 minutes. Training will include how to set up and conduct a WoundView call and optimal wound image capture, such as the use of direct camera angle and adequate lighting to minimize shadow. Nursing home sites will also receive a recording of the training session, quick reference documents, and a site-specific flowchart to integrate WoundView into usual care. A brief training session, including a practice call, will be undertaken with the WCCC staff prior to commencement of the study.

Nursing home staff who participate in training will be invited to undertake a brief, anonymous online evaluation prior to and after the training sessions. The trainer will describe the survey, display a QR code for the survey, and leave the room to allow participants to decide whether to complete the survey. The number of nursing home staff participants is expected to be 10 to 30.

In Phase 2, nursing home staff, WCCC clinicians, and usual wound care providers will be invited to participate in a brief online survey and an in-depth, semistructured interview with a member of the research team lasting approximately 20 to 30 minutes. Nursing home management will be asked to assist by making staff aware of the study through email correspondence or posting advertisements in appropriate locations, such as staffrooms. WCCC clinicians and usual wound care providers will be invited to participate through email correspondence. The survey will be accessible online along with the Participant Information Statement and consent form. Those interested in being interviewed will be able to self-identify at the end of the survey or initiate contact with the research team to arrange an interview. The number of survey participants is expected to be 5 to 10, and interview participants are estimated to be 5.

Participants will not receive any payment or reimbursement for their participation. Participants may withdraw from the research study at any time with assurance that their withdrawal will not affect their relationship with their employer or the university. To avoid perceived or actual coercion, written consent of nursing home staff, WCCC clinicians, and usual wound care providers will be undertaken by the research team, who are independent of the nursing home.

### Intervention

The intervention, WoundView, is a novel computer vision–based AI wound analysis application integrated into the Coviu telehealth platform. WoundView is a software component that extends the functionality of the Coviu platform, without requiring changes to its core code. WoundView will link residents with chronic wounds and their clinical care team to specialized wound care clinicians at the WCCC in Sydney, Australia, or their usual wound care providers, who will deliver expert wound care based on clinical data gathered during video telehealth, AI wound analysis, including wound measurements and segmentation, and resident and family preferences.

WoundView requires an initial referral from the participating nursing home to the WCCC or usual care provider for an eligible resident. An appointment is scheduled using the Coviu platform, and the resident, nursing home staff, and wound care clinician attend at the scheduled time. At each use of WoundView, wound image and video data will be gathered by nursing home staff who will take a series of wound photographs prior to or during the WoundView call and submit these for AI wound analysis. The inclusion of an ArUco marker (a marker of known size) in each wound image enables AI wound size analysis using the WoundView AI algorithm. The AI wound analysis provides wound measures such as length, width, and area, along with wound segmentation. Live video stream of the wound will also be available during the call, providing treating clinicians with detailed, close-up vision of the wound, an innovative feature of WoundView. The wound care clinician provides clinical advice about wound management, including cleaning, debridement, dressings, and frequency of dressing change. Further wound review is arranged as advised by the wound care clinician.

### Outcomes

The primary outcome will be a narrative description of study feasibility, including participant recruitment and retention, protocol adherence and adaptations, and stakeholder acceptability (Table 1). A traffic light system will guide progression to an implementation study [37], red (stop, main study not feasible), amber (feasible with modifications or close monitoring), and green (continue without modifications) [38]. A recruitment rate of greater than 50% (defined as the percentage of eligible residents recruited) and retention of greater than 75% (proportion of participants who remain in the pilot for its duration) will be considered acceptable to proceed with the implementation study without modification. Protocol adherence, the degree to which the WoundView intervention and research protocol were implemented as intended, greater than 75% will be considered acceptable. Additionally, regular stakeholder input and agreement on the interpretation of pilot findings will be sought [37]. Acceptability will be assessed by measuring participants’ satisfaction with study assessment instruments, and the use, delivery, barriers, and enablers to the intervention, WoundView. Data collection instruments are described in the section below. Secondary outcomes, including wound measurements, virtual care activity, health-related quality of life (HRQoL), hospitalization rates, health resource use case studies, and patient and staff satisfaction, will be assessed for feasibility of inclusion in a planned implementation study.

**Table 1. T1:** Overview of outcomes and methods.

Outcome levels	Methods and approaches
Primary	
Feasibility	
Recruitment	Percentage of eligible residents recruited
Retention	Proportion of participants who remain in the pilot for its duration
Adherence	Degree to which the WoundView intervention and research protocol were implemented as intended (eg, staff training logs and surveys), WoundView use and activity, resident, staff, and clinician-reported WoundView use
Satisfaction	Pre- and posttraining staff surveys Staff satisfaction survey Short assessment of patient satisfaction In-depth semistructured interviews (residents, nursing home staff, and wound care clinicians) exploring WoundView acceptability
Secondary	
User confidence and skills	Pre- and posttraining staff surveys
Time to 35% reduction in wound area Time to complete healing Percentage area reduction Gross area reduction	Wound measurements (eg, width, length, and area)
WoundView use	Virtual care activity (eg, call participants, guest, or host), length of call (call, time and date), and AI wound measurements (eg, length, width, and calculated wound area)
Quality of life	Wound-QoL-14^a^ EQ-5D-5L^b^
Care costs	Hospitalization rates Emergency department attendance rates Health resource use case studies
Adverse events	Wound recurrence Adverse events (eg, death, amputation, infection, hospitalization, ED^c^ attendance, and allergic reactions).

a Wound-QoL-14: Wound Quality of Life-14.

b EQ-5D-5L: EuroQoL-5 Dimensions-5 Levels.

c ED: emergency department.

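### The recruitment go criterion divides by eligible residents, but the protocol defines that group in conflicting ways, and under one definition refusals are not counted

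*Protocol article*

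**What the plan says.** Under Outcomes the protocol states: "A recruitment rate of greater than 50% (defined as the percentage of eligible residents recruited"). Exceeding this, together with retention above 75%, "will be considered acceptable to proceed with the implementation study without modification". Table 1 and the Feasibility subsection repeat the definition of the rate without adding to it.

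Three places bear on who counts as eligible:

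- **Textbox 1** is the formal list. One of its four inclusion criteria is that the resident is both willing and able to consent.
- **The recruitment procedure**, in the text after Figure 3, begins: "Nursing home staff and managers will be asked to identify residents who meet the study eligibility criteria (Textbox 1"). The research team approaches the resident only after that, and asks for a preference after a 3-day cooling-off period.
- **The opening of the Residents subsection** says that all residents at the sites "who have or develop a chronic wound during the study period, regardless of wound type, will be eligible to participate". It sets no consent condition there. Study Design likewise calls all residents with a chronic wound eligible to receive the intervention.

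On sampling, the Residents subsection says: "Recruitment will be undertaken using purposive sampling, where participants who meet the eligibility criteria will be consecutively enrolled into the study". The same subsection estimates 6 to 10 resident participants, and the Abstract says: "The research population will comprise up to 10 nursing home residents". The article states no expected number of eligible residents and no expected number of refusals.

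**The concern.** Recruitment is part of the primary outcome and has a numeric rule attached. Its main use is to show whether enough suitable residents agree to take part. If willingness is a condition of being eligible, a resident who declines leaves the denominator, and the rate no longer measures agreement. If eligibility is judged before the approach, the same resident stays in and the rate is informative. The protocol supports both, and the wider description of all residents with a chronic wound gives a third denominator.

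Two further features affect the denominator. Staff decide whom to put forward, so a suitable resident whom they hold back may never be counted. The sampling is also called both purposive and consecutive. A recruitment rate can be interpreted under consecutive enrolment, but not if candidates are picked purposively.

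At stake is whether the implementation study is planned without modification on an uptake figure that depends on which definition was used. First participants were recruited in May 2025 (Results section), so an undefined denominator could be settled after the numerator is known.

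**Working it through.** The plan has no calculation to reproduce. The 6 to 10 residents are an estimate given without a formula or denominator, and 50% is a chosen threshold.

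**Inputs from the protocol.** Threshold: rate above 50% (Outcomes). Recruits R: 6 to 10 (Residents).

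**Assumed inputs, not in the protocol.** N, the residents who meet every criterion other than willingness: 12 to 20. Acceptance p: 20% to 70%, independent between residents.

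**Step 1. The same recruitment under two definitions, with R = 6 and N = 20.**

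- Textbox 1 taken literally, so refusers are not eligible: rate = R/R = 6/6 = 100%, green.
- Criteria applied before the approach, so refusers are kept: rate = R/N = 6/20 = 30%, not green.
- All residents with a chronic wound: the denominator is at least N, so the rate is at most 30%. How much lower cannot be computed from the document.

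**Step 2. What the threshold demands when refusers are kept.** R/N > 0.5 requires N < 2R, so N is at most 2R − 1. That is 11 for 6 recruits, 15 for 8 and 19 for 10.

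**Step 3. Chance of exceeding 50%.** With refusers kept, this is P(X ≥ N/2 + 1) for X binomial(N, p). With refusers dropped, the rate is about 100% as soon as one resident is recruited, so the chance is about 1 − (1 − p)^N.

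| p | N = 12, kept | N = 12, dropped | N = 20, kept | N = 20, dropped |
|---|---|---|---|---|
| 20% | 0.004 | 0.931 | 0.001 | 0.988 |
| 30% | 0.039 | 0.986 | 0.017 | 0.999 |
| 40% | 0.158 | 0.998 | 0.128 | 1.000 |
| 50% | 0.387 | 1.000 | 0.412 | 1.000 |
| 60% | 0.665 | 1.000 | 0.755 | 1.000 |
| 70% | 0.882 | 1.000 | 0.952 | 1.000 |

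With refusers kept, the rule separates poor from good uptake. With refusers dropped, it hardly does so at all.

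**Step 4. Residents not put forward.** Take again 6 recruits among 20 otherwise-eligible residents. If staff do not put forward 9 of the 20 and these are not counted, the rate is 6/(20 − 9) = 6/11 = 54.5%, green, against 30% when they are counted. Here refusers are kept, so the effect is separate from the one in Step 1.

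**The case against.** The strongest reply is that the recruitment procedure settles the matter. Staff identify residents as meeting Textbox 1, the approach follows, and preference is ascertained later, so a refuser has already been classed as eligible. A cut-off of 50% also makes little sense unless the authors expected some eligible residents not to be recruited. Moreover, the primary outcome is described as narrative, the traffic light is a guide, and adherence and stakeholder agreement count as well.

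Much of this stands. A reader might infer that the criterion is met by construction. The document does not support that: it is the result of one reading, and the procedure points the other way. Even on the literal reading, a willing resident could be lost before enrolment, for instance through a change in health, so exactly 100% is not guaranteed. The reply still does not remove the ambiguity. The procedure tells staff to apply Textbox 1, which contains a willingness criterion that is not established until after the approach, and no section says which group is the denominator.

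Two other inferences go too far:

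- A reader might take the Abstract's upper figure of 10 as an enrolment limit that makes the criterion fail once there are 20 eligible residents (10/20 = 50.0%, against 10/19 = 52.6%). The Residents subsection calls 6 to 10 an estimate and says "participants who meet the eligibility criteria will be consecutively enrolled into the study". Nothing states that enrolment stops at 10.
- A reader might multiply the sites' beds by the pressure-injury prevalence in the Introduction to get a denominator. That prevalence is an upper figure for one wound type, before any eligibility criterion is applied. It is not a count of eligible residents.

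Calling the sampling purposive may be loose wording, since the sentence goes on to describe consecutive enrolment. It costs nothing to correct.

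**Conclusion.** The point holds as an inconsistent denominator for a primary progression criterion. One written definition makes the criterion nearly uninformative about refusal; another keeps it informative. For the assumed 6 of 20, the reported rate is 30% or 100%. For assumed acceptance of 30% with 12 to 20 otherwise-eligible residents, the chance of exceeding 50% is 0.039 to 0.017 with refusers kept and 0.986 to 0.999 with them dropped. These sizes rest on assumed values of N and p, because the protocol gives neither. The conflict between sections does not depend on them.

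Uncounted residents whom staff hold back are a possibility, not an established loss: the article does not say how they are recorded. The matter should be settled before the recruitment rate is analysed. It is a clarification of a stated rule and does not show that the study cannot assess recruitment.

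**What to change.** In Outcomes, Feasibility and Table 1, use one definition: recruitment rate = residents who consent / residents who meet all Textbox 1 criteria other than willingness to consent. Ability to consent stays a criterion.

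- Take the denominator from a screening log of residents with a chronic wound at both sites during the enrolment window.
- Keep otherwise-eligible residents who declined, and those not put forward by staff, in the denominator, and report each count separately.
- In the Residents subsection, replace purposive with consecutive.
- If 10 is a true enrolment limit, say so and close the denominator on the date it is reached. If it is only an estimate, make the Abstract agree with the Residents subsection.

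The cost is a few lines of wording and a short log; the 50% threshold can stay. The reported rate may be lower. Because recruitment has begun, part of the log may have to be rebuilt from site wound records. The Introduction itself cites incomplete wound documentation in nursing homes, so any rebuilt part should be marked as such.
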